## Abstract

**Background:**

Multiple sclerosis (MS) is the most common demyelinating disease of the central nervous system. Over the past years, spinal cord MRI (SC-MRI) has improved significantly in quality and has become an important part of the diagnostic workup for MS. Presently, follow-up imaging of the spinal cord is mainly performed when spinal cord related symptoms occur. However, there is increasing evidence that asymptomatic cord lesions can occur independently of brain disease activity. Even asymptomatic spinal cord lesions have been shown to be a poor prognostic factor regarding future disability accrual. Additionally, the association between (asymptomatic) spinal cord lesions and progression independent of relapse activity (PIRA) remains undefined. Prospective data on the frequency and importance of asymptomatic spinal cord lesions, and therefore the potential role of SC-MRI in treatment monitoring, is lacking.

**Objective:**

We will routinely scan the whole spinal cord (as well as routine brain MRI) to prospectively collect SC-MRI data, in addition to clinical parameters, blood-biomarkers and CSF, in recently diagnosed MS patients. The goal is to assess the incidence of asymptomatic spinal cord lesions in patients commencing disease modifying treatment (DMT) for the first time. It will be assessed how often disease activity is solely proven by SC-MRI. A secondary objective is to identify patient groups predisposed to developing new spinal cord lesions during follow-up in early disease.

**Methods:**

This will be a multicentre, prospective longitudinal, observational study. The study population consists of relapsing-remitting MS patients, between 18 and 65 years old, initiating their first DMT within 5 years of the first clinical event. We aim to include 155 patients, who will receive three yearly SC-MRI (both sagittal and axial), brain MRI and biomarker assays during follow-up of 27 months.

**Results:**

This study started in August 2024. Currently, inclusion is still ongoing.

**Conclusions:**

The goal of this study is to explore the incidence of asymptomatic spinal cord lesions in early MS and to identify prognostic factors for spinal cord disease activity.

**Trial registration:**

This study has been registered in the Dutch CCMO/OMON Registry under **NL-005846** at 12/03/2024 (https://onderzoekmetmensen.nl/nl/trial/56629) and in ClinicalTrials.gov under registration number **NCT06827834.**

## Introduction

### Background and rationale

Multiple sclerosis (MS) is an immune-mediated inflammatory disease affecting the brain and spinal cord, causing neurological complaints and physical disability. Spinal cord MS lesions, including asymptomatic lesions, have been identified as a prognostic factor for conversion of a clinically isolated attack to clinically definite MS, for development of progressive MS and for higher levels of sustained clinical disability in the long term [2, 22]. It is debatable whether generalised and widely used study findings on prognostic markers and treatment effect using brain MRI outcomes in MS can be extrapolated to the spinal cord. Several observations support this doubt:

Firstly, the spinal cord differs from the brain, not just anatomically (volume, white/grey matter organisation, vascularization), but also in barrier functions; the composition and function of the blood-spinal cord barrier are distinct from the blood-brain barrier. Secondly, immunological characteristics (certain lymphocyte subsets and cytokine profiles which influence localization of inflammatory activity) may also differ in the spinal cord. Last- and most importantly, MRI studies suggest that brain and cord pathology radiologically progress independently [13].

In clinical practice, spinal cord MRI (SC-MRI) is mostly performed in case of possible cord-related symptoms or unexplained clinical progression, while brain MRI is performed in standard follow-up to assess radiological progression of disease. Although most spinal cord lesions are clinically symptomatic, it was reported that new spinal cord lesions may occur in absence of clinical signs or symptoms (31.2% of all reported SC-lesions), even independently of brain MRI activity (12.1%) [8]. Additionally, little is known about the effect of disease-modifying treatment (DMT) on spinal cord lesions [13].

A commonly used outcome measure in MS drug trials is ’no evidence of disease activity’ (NEDA). NEDA-3 is defined as no relapses, no disability progression, and no new radiological activity on MRI. Regarding the latter, in almost every MS drug trial, only brain and not SC-MRI is included [16], with retrospective studies showing contrasting results regarding the value of adding SC-MRI in NEDA evaluation [6, 21]. However, inherent to the retrospective design of these studies, they suffer from selection bias. In a study investigating NEDA in a large cohort of MS patients using first- as well as second-line treatments, every year there were 8% − 12% more patients showing evidence of disease activity solely based on SC-MRI [20].

A recently introduced concept in MS is progression independent of relapse activity (PIRA) and/or progression independent of relapse and MRI activity (PIRMA), highlighting the significance of clinical disability progression that occurs regardless of relapse events or MRI findings. PIRA/PIRMA represents the proposed pathological mechanism of chronic neurodegeneration in MS as opposed to acute inflammation associated with relapse.

Evidence on the contribution of spinal cord lesions, particularly asymptomatic lesions, to PIRA/PIRMA remains scarce, largely due to the omission of routine spinal cord imaging in standard MRI protocols. Given that asymptomatic spinal cord lesions have been implicated in disability progression, insufficient monitoring of the spinal cord may lead to an underestimation of their potential role in the PIRA/PIRMA mechanism [4]. The operational definition of PIRMA may possibly require expansion to incorporate routine spinal cord MRI monitoring, thereby capturing asymptomatic spinal cord lesions that could otherwise confound assessments of progression independent of relapse and (brain) MRI activity.

We reported previously in a retrospective setting, that approximately a quarter of patients under a DMT developed new spinal cord lesions in the first 3 years after starting treatment (see Fig. 1) [11]. Other reports estimate that about 10–25% of spinal cord lesions are asymptomatic and therefore are missed when SC-MRI is not part of routine follow-up after starting a DMT [3, 22].

Given that (asymptomatic) spinal cord lesions may occur with some frequency, possibly remain undetected in current follow-up regimens, and are not accounted for in the outcome measures of clinical drug trials—yet may have implications for future disability—an important question arises: should routine spinal cord follow-up be incorporated into standard clinical practice?

This study seeks to determine the frequency of asymptomatic spinal cord lesions in patients with early MS initiating their first disease-modifying treatment, and to evaluate whether spinal cord MRI detects disease activity not captured by clinical assessment or brain MRI alone.

**Fig. 1 Fig1:**
[figure not shown]
New spinal cord lesions in patients receiving DMT (> 90% of follow-up duration low-efficacy DMT or > 90% of duration high-efficacy DMT) from a retrospective cohort (Zuyderland MC) of patients that underwent > 1 SC-MRI during follow-up. Adapted from Kreiter et al. [11].

### Spinal cord-disease prone subgroups

As described above, adding SC-MRI to routine follow-up in MS patients could bring several advantages and opportunities. However, incorporating routine spinal cord imaging into follow-up protocols for all MS patients presents several disadvantages. It significantly prolongs the scanning protocol, with consequently adding considerable costs and burden on the often-scarce MRI scanning capacity. Furthermore, extended MRI scanning times impose a greater burden on patients. Ideally, subgroups can be identified that are prone to more spinal cord involvement and that would benefit from routine spinal imaging. To this end, increasing our understanding of factors that contribute to spinal cord pathology in MS is needed.

Currently, the relationship between baseline patient characteristics and radiological, biochemical, and genetic markers with new spinal cord disease activity remains poorly defined. Cross-sectional studies have demonstrated some associations: for instance, certain cerebrospinal fluid (CSF) profiles—particularly intrathecal IgM synthesis—have been linked to spinal cord lesions. Whether intrathecal IgM synthesis also predicts more spinal cord involvement at follow-up is unknown. Additionally, MS patients with the HLA-DRB1*1501 allele show more extensive spinal cord pathology in cross-sectional studies [13].

From a clinical perspective, the initial presenting syndrome, such as optic neuritis or myelitis, may be relevant for identifying patients with a higher likelihood of significant future spinal cord involvement. From a radiological standpoint, the presence of spinal cord lesions early in the disease course could serve as a potential indicator of spinal cord-predominant disease and may warrant consideration for routine spinal cord imaging follow-up. Other markers that could be of interest in the context of selecting patients with risk of spinal cord demyelination are blood markers that have previously been associated with an increased risk of disease progression. The specific relation of these markers to spinal cord demyelination is yet to be determined.

The following blood biomarkers are specifically of interest; low baseline 25-hydroxyvitamin D level [1], high neurofilament light chain (NfL) levels and glial fibrillary acidic protein (GFAP) [5], which have been associated with disease activity on cerebral MRI and disability progression.

Additionally, plasma-based immunological biomarkers could be promising candidates. For example, within the group of soluble immune checkpoint markers (sICPs) multiple markers, such as soluble IL-2, soluble CD27, soluble CD14, soluble B cell maturation antigen, soluble TREM-2, have been identified as elevated in MS patients and correlate with signs of clinical and/or brain MRI disease activity [14, 15]. Their association with spinal cord lesions is not yet known.

It was also found that patients treated with interferon-beta without brain MRI activity tend to have a favourable level of transitional B cells [17], but their association with progression/activity on SC-MRI is to be determined. From experimental autoimmune encephalomyelitis (EAE) experiments there is evidence that the balance between CD4 + T cell subsets and their cytokine profiles influence spatial localization of inflammatory activity. The balance between Th1 and Th17 cells is thought to determine whether there is more brain or spinal cord inflammation, foremost mediated by IFN-γ and IL-17 [7], suggesting that immunological markers are possible candidates for predicting more spinal cord involvement.

## Methods

### Aim of the trial

The primary objective of this study is to prospectively collect both full sagittal and axial SC-MRI data (in addition to routine brain MRI), in recently diagnosed MS patients, to address the following research questions:

What is the incidence of asymptomatic spinal cord lesions in patients commencing DMT? How frequently do asymptomatic spinal cord lesions occur in absence of radiological progression on brain imaging? In other words, how often is disease activity solely proven by SC-MRI and what is the number-needed-to-scan?

The secondary objective is to investigate which patients are predisposed to developing new spinal cord lesions during follow-up in early disease stages. Regarding this question, the primary focus will be on factors such as CSF profiles, lymphocyte composition in blood, blood biomarkers and clinical features.

We hypothesize that the detected incidence of asymptomatic cord lesions independent of brain MRI activity will be higher than the approximately 10% per year reported in retrospective studies [8, 20]. Additionally, we expect that more SC lesions occur in a subgroup of MS patients with CSF profile positive for intrathecal IgM, IgG synthesis and higher number of oligoclonal bands, a low number of transitional B cells at baseline, increased or decreased levels of sICPs at baseline, and/or a presenting clinical syndrome of optic neuritis or myelitis.

### Study description and study design

#### Outcomes and participant timeline

The follow-up period will be 27 months and visits will take place at approximately 3, 15 and 27 months. At these follow-up moments, next to routine yearly brain MRI, spinal cord coverage will be added to the scan protocol.

During the follow up visits, routine consultation with a standard medical history, a questionnaire regarding potential urinary tract symptoms, additional clinical tests/parameters, and additional blood collection will be performed. Figure 2 gives a concise overview of study procedures during the follow up period.

**Fig. 2 Fig2:**
[figure not shown]
Overview of study timeline and collected data. See supplementary material for additional concise information

*At baseline*,* the following characteristics will be registered: age*,* sex*,* height and weight (body mass index)*,* comorbidities*,* cerebrospinal fluid data (if lumbar puncture took place as part of the diagnostic workup)*,* presenting syndrome*,* disease duration*,* family history of MS*,* previously performed cerebral and SC-MRI data.*

*Furthermore*,* MS related relapses*,* extra outpatient clinic visits*,* clinical testing and performed MRI scans of brain or spinal cord will be registered in the study as additional visits and scans*.

### Outcome measures

Full inclusion is sought to be achieved by mid-2026 which will result in the ending of the data collection mid-2028. It is expected that data analysis and subsequent publication of results will follow in the second half of 2028. The following study parameters are measured during study conduction.

#### MRI

During follow-up the SC-MRI-scans are performed in addition to the brain MRI. As explained in Table 1, MRI protocol will contain sagittal as well as axial sequences of the complete spinal cord. MRI-images will be assessed and reported by a local radiologist of the participating centres for clinical purposes. The images and reports will then be exported and pseudonymised and are then reviewed by a second neuroradiologist who is part of the study team. The primary and secondary reports will be compared to assess interobserver reliability. If first and second reports differ, a third neuroradiologist will be consulted for arbitration after assessment of the previous reports and images. Gadolinium-based contrast agents will not be used for routine follow-up imaging, in accordance with current guidelines. Contrast enhancement rarely adds clinically relevant information for longitudinal assessment, does not change therapeutic decision-making, may even influence volumetric measurements, and carries cumulative exposure considerations (Pawlitzki et al., [18, 19].

**Table 1 Tab1:** MRI protocol

MRI protocol	Brain MRI	Spinal Cord MRI
Scanner	Preferably 3 T MRI (if unavailable, the same MRI scanner, e.g. 1.5T, should be consistently used per subject)	
Sequences	Local routine MS follow-up brain protocol including at least an axial FLAIR	**Sagittal**: T1 (3 mm), T2 (3 mm), STIR (3 mm) (Cervical, Thoracic, Conus Medullaris) **Axial**: T2* MEDIC (3 mm) [C0-C7], T2 TSE (4 mm) [C0-L1]

In line with current MS diagnostic and treatment guidelines, all patients will have had a recent brain and SC-MRI prior to DMT initiation, either diagnostically or due to disease activity prompting treatment. These pre-treatment MRIs will be collected retrospectively and included in the analysis.

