### Statistics

#### Sample size

To estimate the incidence of asymptomatic cord lesions in absence of brain MRI activity, an approximate sample size of 139 will be needed, given an estimated proportion of asymptomatic cord lesions of 10% based on retrospective literature [6, 8, 20] (precision 0.05, confidence level 0.95).

CSF profiles are studied as a priori selected predictor and additionally we provide descriptive data and analyse associations in an exploratory fashion for the other different clinical, radiological, biochemical factors and treatments used in patients with/without new spinal cord lesions, to be able to identify important prognostic candidates, which in turn can be specifically studied in a possible future extension of the study.

Not all collected parameters are included in a prognostic model for spinal cord disease activity, because for the prognostic model to include a wide variety of predictors, a very large population is needed (estimated > 400), which currently is not feasible.

To assess a logistic regression model in which certain CSF profiles (primarily the degree of intrathecal IgM production) are associated with any new spinal cord lesion within two years of follow-up, an estimated sample size of 144 patients is needed to be able to detect an odds ratio of 2 (expected R-squared between main predictor variable and other covariates estimated 0.07 based on retrospective data) with a power of 80%, alpha of 0.05 given that the base expected proportion of patients with new cord lesions within two years is about 15%. The latter figure is based on retrospective data from a local database, where we found that 19% of patients (*n* = 217) developed new cord lesions (regardless of treatment) within 2 years of initiation of a new treatment [11]. In the international MSBase registry this figure was 12% for treatment-naïve RRMS patients starting a DMT (*n* = 528) [12].

Given the calculated sample sizes and an expected loss-to-follow-up of about 2–7% based on other longitudinal prospective MS MRI studies [9, 10], for this study we will aim to include 155 patients.

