### Statistical analysis

#### Primary analysis

The primary objective is to determine the incidence of new asymptomatic spinal cord lesions in the study population. The incidence of new asymptomatic spinal cord lesions will be calculated as the proportion of patients with at least one new lesion at the predefined follow-up timepoints. 95% confidence intervals (CI) will be calculated using exact binomial methods. The relationship between new asymptomatic spinal cord lesions and concurrent brain MRI activity will be assessed to identify lesions occurring independently of brain activity. From these data, the *number needed to scan* (NNS) will be calculated as the inverse of the proportion of patients with isolated asymptomatic spinal cord activity detected at 15 months (T2) and 27 months (T3) after DMT initiation.

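### As worded, the second neuroradiologist receives the local report with the images, so the plan does not secure the independent second read that its reliability and arbitration steps need

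*Protocol article*

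**What the plan says.** The Protocol article (Outcome measures, MRI) describes four steps in order.

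1. First read: "MRI-images will be assessed and reported by a local radiologist of the participating centres for clinical purposes".
2. Transfer and second read: "The images and reports will then be exported and pseudonymised and are then reviewed by a second neuroradiologist", who belongs to the study team.
3. Comparison: "The primary and secondary reports will be compared to assess interobserver reliability".
4. Arbitration: "If first and second reports differ, a third neuroradiologist will be consulted for arbitration after assessment of the previous reports and images".

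The primary endpoint rests on these reads: "The incidence of new asymptomatic spinal cord lesions will be calculated as the proportion of patients with at least one new lesion" (Primary analysis). The same section derives the number needed to scan from isolated asymptomatic cord activity at 15 and 27 months, which also needs the brain read. The Secondary analysis uses any new cord lesion within two years as the outcome of the CSF regression.

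**The concern.** In the second step, the images and the reports together are what the second neuroradiologist reviews. Pseudonymisation hides the patient's identity but not the first reader's findings. The article mentions no masked read, no locked read and no later release of the report.

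Interobserver reliability is meaningful only when each reader reaches a result without the other's. A reader who has the earlier report can be drawn towards it, which raises agreement without raising accuracy. The same mechanism weakens arbitration: because a difference between the reports is the trigger, a local miss or over-call that the second reader follows produces no difference and stays in the data. Those data feed the incidence, the number needed to scan and the regression outcome.

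**Working it through.** **The plan's own figure.** The Sample size section works from "given an estimated proportion of asymptomatic cord lesions of 10% based on retrospective literature" ("precision 0.05, confidence level 0.95"). The single-proportion formula gives n = 1.96² × 0.10 × 0.90 / 0.05² = 138.3, rounded up to 139, as stated. This point does not dispute that figure. It shows only how few events are expected: 0.10 × 139 = 13.9, about 14 patients.

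**Inputs that the document does not give.** It reports no reader accuracy and no measure of how far a second reader would follow a report. Both are assumed here:
- sensitivity/specificity, equal for both readers: 0.70/0.95, 0.80/0.97 and 0.90/0.98;
- share *a* of second reads that copy the first report: 0, 25%, 50% and 75%; the rest are independent given the true status;
- true prevalence 10%, with one read per patient. This borrows the planning proportion and simplifies the repeated scans.

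**Formulas.** With prevalence π, sensitivity Se and specificity Sp:
- positive rate of each reader: m = π·Se + (1−π)(1−Sp)
- disagreement: d = 2(1−a)[π·Se(1−Se) + (1−π)·Sp(1−Sp)]
- chance agreement: pe = m² + (1−m)²
- kappa = (1 − d − pe)/(1 − pe)
- share of first-reader errors that produce a difference: (1−a)[π(1−Se)Se + (1−π)(1−Sp)Sp] / [π(1−Se) + (1−π)(1−Sp)]

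**Worked example, 0.80/0.97.** m = 0.080 + 0.027 = 0.107 and pe = 0.107² + 0.893² = 0.8089. The bracket in d is 0.0160 + 0.02619 = 0.04219.
- a = 0: d = 0.0844, kappa = (0.9156 − 0.8089)/0.1911 = 0.56. Errors reaching arbitration: 0.04219/0.047 = 90%.
- a = 0.5: d = 0.0422, kappa = (0.9578 − 0.8089)/0.1911 = 0.78. Errors reaching arbitration: 45%.

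**All scenarios** (three values per cell, for 0.70/0.95, 0.80/0.97 and 0.90/0.98):

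| Second reads copying the first | Kappa | First-reader errors reaching arbitration |
|---|---|---|
| 0 | 0.37 / 0.56 / 0.72 | 85% / 90% / 95% |
| 25% | 0.53 / 0.67 / 0.79 | 64% / 67% / 71% |
| 50% | 0.69 / 0.78 / 0.86 | 43% / 45% / 48% |
| 75% | 0.84 / 0.89 / 0.93 | 21% / 22% / 24% |

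Any copying raises kappa and lowers the share of errors arbitrated. The amount follows directly from the assumed *a*.

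**Effect on the incidence.** Let a third reader of the same accuracy settle differences independently. Take Se 0.70 and Sp 0.95.
- a = 0: true positives kept, 0.49 + 0.42 × 0.70 = 0.784; false positives kept, 0.0025 + 0.095 × 0.05 = 0.00725. Estimated proportion: 0.1 × 0.784 + 0.9 × 0.00725 = 8.5%. Patients misclassified: 0.1 × 0.216 + 0.9 × 0.00725 = 2.8%.
- a = 0.5: true positives kept, 0.595 + 0.21 × 0.70 = 0.742; false positives kept, 0.02625 + 0.0475 × 0.05 = 0.028625. Estimated proportion: 10.0%. Patients misclassified: 0.1 × 0.258 + 0.9 × 0.028625 = 5.2%.

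Here copying nearly doubles the misclassified patients, yet the net proportion lands on the true 10% because misses and over-calls offset. With Se 0.70 and Sp 1.00, the false-positive terms vanish and the estimate goes from 7.8% to 7.4%, the opposite direction. The sign of any bias therefore depends on reader accuracy, which is unknown.

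**Sensitivity to a few patients.** 14/139 = 10.1%, number needed to scan 139/14 = 9.9. Two uncorrected misses give 12/139 = 8.6% and 11.6; two uncorrected over-calls give 16/139 = 11.5% and 8.7.

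**The case against.** The sentence can be read as describing data transfer: the reports must be exported anyway for the later comparison and arbitration. The second reader writes a separate report, access to earlier reports is spelled out only for the third reader, and the word interobserver suggests that separate reads were intended. A journal article may also leave reading order and masking to a full protocol or imaging manual. This stands to the extent that the article does not prove the second reader consults the report first. It does not remove the point, because the sentence as written sends the reports to that reader, and nothing in the article restores independence.

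A reader might infer more than the document supports:
- **That the reads are certainly not independent.** This depends on the order of reading, which is not stated.
- **That arbitration is the plan's only safeguard.** The second read is itself a check, and a reader holding the report can still disagree.
- **That the report reveals whether a lesion is asymptomatic.** The MRI section does not assign that judgement to the radiologists. Relapses, visits and clinical tests are recorded separately (timeline figure legend; Clinical tests). What a local report contains is speculation.
- **That the incidence is biased in a known direction.** Missed and over-called lesions pull in opposite directions.

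Reliability is also not among the stated objectives, so an inflated kappa alone changes no main conclusion. The arbitration route is what touches the primary endpoint. The third reader's access to earlier reports is normal and is not questioned.

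**Conclusion.** The point holds conditionally. The wording passes the local report to the second reader and does not secure a read made before it is seen. If the report is seen first, agreement would tend to be overstated and fewer local errors would reach the third reader. That direction holds in every illustrative scenario with any copying. The size cannot be derived from the document: the kappa and arbitration figures rest wholly on assumed accuracy, prevalence and copying shares. The direction of any bias in the incidence or number needed to scan is likewise undetermined. With about 14 expected events, a few uncorrected reads would be visible in the result, which justifies an inexpensive repair while the study is running.

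**What to change.** Give the second neuroradiologist the pseudonymised images, with prior scans, but not the local report. Have that reader record and lock the cord and brain reads. Then release the local report for the comparison and, where the reports differ, for arbitration.

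The study began in August 2024, so some reads may already have been made with the report in view. Flag these and leave them out of the reliability estimate. Doing so does not repair the primary endpoint, so report them there as not independently read, for example with a sensitivity analysis restricted to independently read scans.

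The cost is a changed export order and a small amount of extra analysis, with no added scans or readers. Inclusion is ongoing and data collection is planned to mid-2028, so later reads can still be protected. If the full protocol already masks the second reader, only the sentence in the article needs correcting.

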### Recruitment and eligibility criteria

We aim to include a population of treatment-naïve RRMS patients, 18–65 years old, early in the disease course, when a first DMT is initiated. Inclusion is performed in five Dutch MS centres; Zuyderland Medical Centre, Erasmus Medical Centre, Jeroen Bosch Hospital, Rijnstate Hospital and Albert Schweitzer hospital. In- and exclusion criteria have been explained in detail in Table 2.

**Table 2 Tab2:** In- and exclusion criteria

Inclusion Criteria	Exclusion Criteria
Diagnosed with RRMS (≤ 5 years since first clinical event)	First clinical event > 5 years ago
Age between 18–65 years	Age < 18 or > 65 years
Treatment-naïve patients starting a currently approved DMT in the Netherlands	Prior DMT initiation
	Incapable of giving informed consent
	Unable to undergo local MRI scan - Physical limitations (e.g., obesity, inability to lie flat) - Claustrophobia
	Contraindications for MRI scan - MRI-unsafe implants/devices (e.g., pacemaker, ocularmetal splinters) - Pregnancy at inclusion

Individual subjects will not be replaced after withdrawal. Sample size calculation has been done with correction for expected loss to follow up. This study does not include any interventions. Patients who choose to withdraw from the study will go back to receiving standard care.

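### Table 1 requires the same scanner per subject only where 3 T is unavailable; for a new-lesion outcome the requirement should cover every subject

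*Protocol article*

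**What the plan says.** The scanner row of Table 1 (Outcome measures, MRI) reads "Preferably 3 T MRI (if unavailable, the same MRI scanner, e.g. 1.5T, should be consistently used per subject". No other sentence in the article sets a scanner condition.

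The outcome is longitudinal. Under Outcomes and participant timeline, "visits will take place at approximately 3, 15 and 27 months". Under Primary analysis, the incidence is "calculated as the proportion of patients with at least one new lesion at the predefined follow-up timepoints", and the number needed to scan (NNS) is the inverse of the proportion with "isolated asymptomatic spinal cord activity detected at 15 months (T2) and 27 months (T3) after DMT initiation". Neither definition says how to treat a lesion first seen after a change of scanner.

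The reading process is a local report, then a second neuroradiologist from the study team. Where they disagree, "If first and second reports differ, a third neuroradiologist will be consulted for arbitration".

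Under Recruitment and eligibility criteria, "Inclusion is performed in five Dutch MS centres".

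**The concern.** The sponsor has accepted that within-subject consistency matters, because it wrote the rule for patients who cannot be scanned at 3 T. It did not extend the rule to the others. Two situations are left open:

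- A patient scanned at 3 T throughout may be put on different 3 T machines at T1, T2 and T3.
- A patient whose 3 T access changes during follow-up falls between the preference for 3 T and the request for consistency, which then conflict.

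A lesion already present at the earlier scan but not visible on it can appear on the later one. It would usually have no accompanying symptoms, so it would fall into the category that the study counts. Availability of machines may differ between the five centres, so any effect may differ by centre too.

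At stake are the primary incidence and the NNS. More patients would not reduce an error of this kind.

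**Working it through.** **The plan's own figure.** Sample size section: expected proportion p = 0.10, precision d = 0.05, 95% confidence. n = 1.96² × p(1 − p) / d² = 3.8416 × 0.09 / 0.0025 = 138.3, rounded up to 139. The stated 139 is reproduced, so ±5 percentage points is a fair yardstick for the size of a bias.

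**Inputs that the documents do not give (assumptions).** s = share of patients whose scanner changes between study scans, 15-30%. q = chance that such a patient shows an existing cord lesion as new, 5-10%. The 10% is planned for cord lesions without brain activity; it is borrowed here for the asymptomatic incidence, for which no separate figure is given.

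**Effect on the incidence.** Only patients without a true event can become false positives, so observed = p + (1 − p) × s × q.

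- Low end: 0.10 + 0.90 × 0.15 × 0.05 = 0.10675, about 10.7%.
- High end: 0.10 + 0.90 × 0.30 × 0.10 = 0.127, or 12.7%.

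The addition is 0.7 to 2.7 points, that is 0.675/5 = 14% to 2.7/5 = 54% of the planned half-width. Adding s × q to 10% without the factor (1 − p) would give 10.75-13% and overstate it.

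Outside that range: s = 10%, q = 5% gives 10.45%; s = 50%, q = 10% gives 14.5%. The effect therefore runs from trivial to nearly the whole planned margin, and the documents do not place the study within it.

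**Why inflation is the likelier direction for the incidence.** A change to a less sensitive acquisition can also hide a true new lesion. If m is the chance of that in a changed patient, the loss is s × p × m and the gain s × (1 − p) × q. They balance at m = 0.90q/0.10 = 9q: 45% for q = 5% and 90% for q = 10%. The gain acts on nine patients in ten, the loss on one in ten.

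**Why the same does not follow for the NNS.** The NNS uses isolated cord activity. Let b be the chance that a changed patient shows falsely new brain activity, and B the share with true brain activity. With independent cord and brain errors, the change in the isolated proportion is s × [(1 − p − B) × q × (1 − b) − p × b]. With B = 0 it is zero at b = 0.9q/(0.9q + 0.1):

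- q = 5%: 0.045/0.145 = 31%.
- q = 10%: 0.09/0.19 = 47%.

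A positive B lowers these thresholds, and so does any tendency of cord and brain errors to occur in the same patient. If every falsely new cord lesion came with a falsely new brain lesion, the gain would be nil and the net effect downward. Only with b = 0 and B = 0 would the NNS move from 10 to 1/0.10675 = 9.4 or 1/0.127 = 7.9. The documents give neither b nor B.

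**The case against.** The strongest case against has four parts.

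- **The clause protects the 1.5 T patient.** A reader might infer that patients will drift from 1.5 T to 3 T. The documents do not support that: a patient followed at 1.5 T because 3 T is unavailable is the one case in which consistency is expressly asked for, and the natural reading is a choice made once and kept. This stands. A later move is an unresolved ambiguity, not a permission. The gap that is plain is between 3 T machines.
- **Nothing says that such lesions count as new.** A reader might infer it from "The incidence of new asymptomatic spinal cord lesions will be calculated as the proportion of patients with at least one new lesion", but the article has no rule either way, and all scans get a second read with arbitration. This stands as far as it goes. Arbitration resolves disagreement between readers, however. A lesion not visible on the earlier scan and visible on the later one may be called new by all of them.
- **The size is assumed, and all of 10.7-12.7% lies within ±5 points of the planned 10%.** This stands.
- **Recording fields and sensitivity analyses belong in an imaging manual, CRF or SAP that is not shown.** This stands for their absence, which is not the criticism here. The point is the rule that Table 1 does state, whose scope is too narrow.

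A further limit: the pre-treatment scans are outside the rule. "These pre-treatment MRIs will be collected retrospectively and included in the analysis", and Table 1 cannot govern scans already made. The article does not say whether they or T1 serve as the reference for a new lesion. The point made here concerns changes between T1, T2 and T3.

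**Conclusion.** The point holds as a cheap improvement. Table 1 states a consistency rule but limits it to patients for whom 3 T is unavailable, and leaves conflicting guidance for a patient whose 3 T access changes.

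The likely consequence is some inflation of the asymptomatic cord-lesion incidence: a true 10% observed as about 10.7-12.7% if 15-30% of patients change scanner and 5-10% of those show a falsely new lesion. Both rates are assumptions.

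A reader might also infer that the NNS is biased downward, or that the error favours the hypothesis of an incidence above about 10% per year. Neither is established. Both concern cord activity without brain activity, and a scanner change can create apparent brain activity as well.

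**What to change.** - Reword the scanner row of Table 1: 3 T is preferred at T1, and the scanner and field strength used at T1 are kept for that subject at T2 and T3, whatever the field strength.
- Record scanner and field strength at each visit, including for patients already enrolled.
- Where a change could not be avoided, flag the pair of scans, and repeat the primary incidence and the NNS without flagged pairs.

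The cost is one table cell, one recorded item per visit and one sensitivity analysis. The downside is slightly less flexible scheduling, and some patients stay on 1.5 T although a 3 T slot later becomes free. Data collection is planned to run to mid-2028, so the rule can still protect many T2 and T3 scans. If few scanners turn out to have changed, the record lets the sponsor show that the estimate is little affected.
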